### Plans to promote participant retention and complete follow-up {18b}

Participants will receive $25 each for completing the baseline surveys and $25 each for completing the post-intervention surveys for a total of $50 per participant. Additional indirect financial incentives for study participation include the possibility of receiving benefits from financial aid resources. Participant benefits also include an improved patient care experience and potentially higher retention in oncology care as a result of taking part in the intervention and reducing financial barriers to care.

### Data management {19}

All participant data will be collected and managed via each site’s individual REDCap database, including all baseline surveys, intake forms, check-in forms, and end of study surveys. Medical record data will be abstracted by the trained financial navigator from the site’s electronic medical record and entered into REDCap as needed, such as treatment status and appointment information.

### Confidentiality {27}

The research team is committed to the confidential preservation of data and monitoring of safety of participants. All intervention tracking data and research data will be stored in REDCap, a secure data storage platform made available to UNC researchers through the North Carolina Translational and Clinical Sciences Institute. Site-specific REDCap logins prevent site staff from viewing any other site’s participant information other than their own via REDCap. Only the PIs, study coordinator, research assistant, and financial navigator who are all involved in participant recruitment and data collection will know the identity of the participants and will have access to records in the REDCap database. The PIs, study coordinator, and research assistant will be able to see enrollment in the REDCap database to ensure patient enrollment forms are complete.

To prevent a breach of confidentiality, all identifying participant information will be kept on a secure research database only accessible by sites treating those specific participants, and all de-identified research data are similarly stored on a secure research database to which only the UNC investigators have access. All investigators and site staff working on the study are CITI-certified and will be required to sign a statement promising to maintain all information strictly confidential. To conduct the intervention described above, relevant identifiable participant information will be collected upon enrollment into the study by individual site staff. These data include information such as name, date of birth, and contact information (telephone number, e-mail address). During the FN appointments, participants will provide private information to their navigator. Participants will also complete surveys at two time points during the study; however, these data are not directly linked with identifying participant information.

Data will only be transmitted via UNC's secure network and stored in our Microsoft Teams folders or transmitted among research personnel within the office environment (study meetings). Data transmitted between the server and end-users will be encrypted using SSL, and all databases will be encrypted. As stated previously, all electronic data will be kept in REDCap, which is a secure web application that is used to build and manage case report forms, surveys, and other data capture mechanisms for clinical research. REDCap has been approved by UNC as a secure location for storing sensitive research data.

### Plans for collection, laboratory evaluation, and storage of biological specimens for genetic or molecular analysis in this trial/future use {33}

Not applicable—this trial will not collect biological specimens.

## Statistical methods

### Statistical methods for primary and secondary outcomes {20a}

#### Implementation determinants and outcomes

We will use a CFIR-derived template analysis to develop themes from post-implementation interviews with navigators and stakeholders [33]. We will produce practice-specific and general summaries of findings in a matrix format, following prior work [29]. In addition, we will use standardized barrier/facilitator ratings (ranging from −2 to +2) based upon coded interview data to score the extent to which CFIR-derived constructs were viewed as impediments or accelerants to FN implementation. We will assess and describe FN fidelity using a checklist and the range in uptake and costs across practices.

#### Patient outcomes

We will assess mean pre-/post-FN intervention FT (operationalized as COST scores) using a paired two-sided sample t-test to test the null hypothesis that FN does not result in statistically significant changes in FT, at an alpha level = 0.05. We will again use a paired two-sided sample *t*-test to test the null hypothesis that FN does not result in statistically significant changes in HRQoL, at an alpha level = 0.05. We will use a paired McNemar chi-squared test to test the null hypothesis that the probability of foregoing or delaying care is reduced post-FN is the same as the probability that foregoing or delaying care is increased post-FN.

### Interim analyses {21b}

We will conduct preliminary analyses at 100 patients enrolled and 200 patients enrolled to ensure data completeness and to understand intervention implementation.

### Methods for additional analyses (e.g., subgroup analyses) {20b}

We will assess geographic (rural vs. non-rural) differences in our outcomes, and where feasible (depending on sample sizes within subgroups), racial/ethnic, gender, and age-specific effect modification for the main participant outcome of pre/post-FN change in FT.

### Methods in analysis to handle protocol non-adherence and any statistical methods to handle missing data {20c}

We plan to compare characteristics between participants who do and do not complete follow-up measures and report on any differences to inform additional analyses. Because final primary outcome analyses must compare pre/post differences in FT among participants completing both the baseline and follow-up surveys, we will exclude participants who are missing follow-up survey data.

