### Sample size {14}

We anticipate enrolling a total of 780 participants into the study in order to include 700 participants in the final analysis, allowing for attrition of up to 10%. We aim to include approximately 100 participants in the final analysis per rural site and 50 participants per non-rural site. We considered a very conservative pre/post-FN intervention effect (difference in COST scores) as small as 0.5 as well as a more considerable intervention effect as large as 3.0. A one-sample paired t-test (pre-/post- analysis of the change in COST FT score) with alpha=.05, will have 80% power to detect an effect size of 0.106. This may be seen with an average difference of 1 point, and a standard deviation of 9.43, or a mean difference of 3 points, and a standard deviation of 28.29. Notably, the UNC pilot project on which this study is based found a nearly 7-point improvement in COST FT score post-FN intervention completion.

Given our 2% (1/50) attrition rate for the UNC pilot project this study is based on [32], we do not expect much attrition. If participants are lost to follow-up between consent and their first FN visit, we will replace them since they did not receive the intervention.

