## Data collection and management

### Plans for assessment and collection of outcomes {18a}

After obtaining informed consent, each participant will be assigned a unique study identifier, and then proceed to complete the COST measure. If eligible (i.e., if scoring 22 or less on the COST instrument), participants will then complete the baseline patient experience survey (Additional file 3) and patient outcomes survey. Together these surveys are expected to take less than 30 minutes. Patient outcomes will be assessed using the PROMIS Global Health scale v1.2, PROMIS Emotional Distress-Anxiety – Short Form 6a v1.0, PROMIS Emotional Distress-Depression – Short Form 4a v1.0, and the PROMIS Psychosocial Illness Impact-Positive–Short Form 4a v1.0. The baseline patient experience survey will assess patients’ care-altering behaviors, employment disruption, caregiver cost burden, and the impacts of COVID-19. Following the completion of these surveys, participants will receive an appointment with the financial navigator. During the first FN appointment, financial navigators will complete a comprehensive intake form with the patient (Additional file 4). At all subsequent FN appointments, financial navigators will complete a follow-up check-in form with the patient (Additional file 5). Two to three months after the last FN visit, patients will complete the follow-up survey (Additional file 6), COST measure, and patient outcomes survey. The follow-up survey will include a post-intervention patient experience survey and participant perspectives on FN acceptability (including convenience, accessibility, and satisfaction), responsiveness and alignment with needs, patient-centeredness, and timeliness.

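### The primary analysis drops everyone without a follow-up survey as if it had to, although the mean change can be estimated in all eligible participants with a baseline COST score

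*Protocol article*

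**What the plan says.** The section on non-adherence and missing data {20c} fixes the rule. The reason given is "Because final primary outcome analyses must compare pre/post differences in FT among participants completing both the baseline and follow-up surveys", and the consequence is "we will exclude participants who are missing follow-up survey data". The one safeguard is a plan to "compare characteristics between participants who do and do not complete follow-up measures and report on any differences to inform additional analyses"; those additional analyses are not named.

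The sample size section {14} enrols 780 "in order to include 700 participants in the final analysis, allowing for attrition of up to 10" per cent, and describes the expected loss as small: "Given our 2% (1/50) attrition rate for the UNC pilot project". It also has a separate rule, with its own reason: "If participants are lost to follow-up between consent and their first FN visit, we will replace them since they did not receive the intervention".

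The section on collection of outcomes {18a} gives the order of events. COST and the baseline surveys come first, and then: "Following the completion of these surveys, participants will receive an appointment with the financial navigator". Table 2 lists the socio-demographic variables as collected before the intervention.

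**The concern.** The word *must* is not a real constraint. It is true of the paired t-test named in {20a}, but not of the quantity that the trial wants, the mean change in COST. Section {18a} implies that a baseline COST score normally exists for every eligible participant, including those who never return a follow-up survey. Site and the baseline socio-demographics are also known. A likelihood-based repeated-measures model or multiple imputation can use all of these.

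The choice matters because the two approaches need different assumptions. The complete-case mean change is unbiased for all eligible participants only if completers and non-completers would have had the same average change. A model that conditions on baseline COST and covariates needs this only within levels of those variables. With no control arm, any selection among those who return goes directly into the primary estimate. Follow-up comes 2 to 3 months after a programme lasting 2 weeks to 6 months, and the trial admits people with advanced disease, so selective loss is plausible. Comparing the characteristics of completers and non-completers would show a difference but would leave the estimate unchanged.

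**Working it through.** **Step 1. The plan's own figures.** Inputs from {14}: 700 analysed, alpha 0.05, standardised effect 0.106, with 1 point and SD 9.43 as one illustration. A two-sided paired t-test (noncentral t) with n = 700 and effect 0.106 has power 79.97%, against "with alpha=.05, will have 80% power to detect an effect size of 0.106". 1/9.43 = 0.106. Enrolment: 700/0.90 = 778, against 780 stated; the implied loss is 80/780 = 10.3%. The sample size reproduces and is not at issue.

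**Step 2. Loss that depends only on baseline COST.** The documents give no figures for this, so all inputs here are assumptions: SD 10 at each time, correlation 0.6 between baseline and follow-up, true shift 3 points, population mean 22 (the article's figure) or 15, baseline restricted to the eligible range 0 to 22, and log-odds of loss changing by 0.1 per COST point. The expected change then falls by 1 − 0.6 = 0.4 points per baseline point, so

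bias = −0.4 × (mean baseline of completers − mean baseline of all).

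Example, mean 22 and 10% loss: the mean baseline of all is 14.53. If the worst-off (low COST) are lost more often, completers average 14.84 and the bias is −0.4 × 0.31 = −0.12. If the better-off are lost more often, completers average 14.30 and the bias is −0.4 × (−0.23) = +0.09 (simulated +0.10).

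| Loss | Worst-off lost more often | Better-off lost more often | After regression on baseline |
|---|---|---|---|
| 10% | −0.12 to −0.13 | +0.10 to +0.12 | about 0 |
| 20% | −0.24 to −0.26 | +0.19 to +0.24 | about 0 |

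The ranges cover the two population means. This part of the bias has either sign and is removable.

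**Step 3. Loss that depends on the unobserved outcome.** The mean over all is (1 − m) × completer mean + m × non-completer mean, so

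bias = m × (completer mean − non-completer mean).

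The gap is assumed at 3, 5 or 7 points in favour of completers; a gap the other way reverses the sign. The last column is the two-sided rejection rate if the true change over all is zero, with SD 9.43 and the remaining n out of 780.

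| Loss m | Bias for gap 3, 5, 7 | Rejection rate (nominal 5%) |
|---|---|---|
| 2% (pilot) | 0.06, 0.10, 0.14 | 5.4%, 6.0%, 6.9% |
| 10.3% (planned) | 0.31, 0.51, 0.72 | 14%, 30%, 52% |
| 20% (twice the plan) | 0.60, 1.00, 1.40 | 36%, 75%, 96% |

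**Step 4. Scale.** The article considers effects from 0.5 to 3.0 points and cites a pilot improvement of nearly 7. At planned loss, a 5-point gap gives a bias equal to the smallest effect considered. If instead completers improve by 7 and 10% are missing with no change, the mean over all is 0.9 × 7 = 6.3. To bring it to zero the missing would have to change by −(0.9 × 7)/0.1 = −63 points, which a 0 to 44 scale does not allow.

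**The case against.** The strongest reply has four parts.

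*The fix does not reach the bias that worries people most.* If those lost are the ones who became sicker or gained nothing, imputation from baseline variables does not recover their outcome. This stands: only the step 2 bias is removable. The step 3 bias can be displayed, not removed.

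*The conclusion may well not change.* The plan budgets for 10% loss against 2% in the pilot. With completers at +3 and SD 9.43, the standard error is 9.43/√700 = 0.356 and t is 3/0.356 = 8.4. If the missing 10% worsened by 3, the mean is 0.9 × 3 + 0.1 × (−3) = 2.4, and t is still about 2.4/0.356 = 6.7. This also stands, and limits the point to small true effects or loss at or above the planned level.

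*The target is what happens to people who complete the programme.* The Discussion does describe within-person improvement after programme completion. But programme completion and return of a survey 2 to 3 months later are different events. The exclusion rule turns on the second, so that target does not justify it.

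*Details belong in the analysis plan.* The unnamed additional analyses could well be there. The exclusion and its reason, however, are stated in the article itself.

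A reader might also infer that navigation will look better than it was. The documents do not support a direction: section {11b} lets participants stop because their needs have been met, step 2 shows either sign, and stopping navigation is not the same as missing the survey. Nor is the replacement rule justified by the same *must*. It has its own stated ground, and {14} does not say that replaced participants' data are deleted.

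**Conclusion.** The point holds in a limited form. The exclusion is presented as unavoidable and is not, so the primary estimate rests on a stronger assumption about missing data than necessary. Under the assumptions of step 2, the avoidable bias is about 0.1 points at 10% loss and 0.2 to 0.3 at 20%, in either direction. Under the assumed gaps of step 3, a further 0.3 to 0.7 points is possible at planned loss, and no analysis can remove it. Both are negligible at the pilot's 2% loss. They matter mainly if loss reaches 10% or more, or if the true effect is near 0.5 to 1 point. It would go too far to say that a positive result could not be trusted: an effect near the pilot's would survive planned loss. This is worth changing because the change is cheap, not because the trial is unsound without it.

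**What to change.** 1. Replace the exclusion sentence in {20c}. Make the primary estimate the mean change in eligible participants with a baseline COST score, from a likelihood-based repeated-measures model or multiple imputation using baseline COST, site and the baseline socio-demographics in Table 2. State the missing-at-random assumption.
2. Keep the complete-case paired t-test as a supportive analysis.
3. Add a delta-adjusted (tipping-point) analysis showing how much worse non-completers would have to do before the conclusion changes.
4. Treat the replacement rule in {14} separately. Keep the baseline data of replaced participants, report their number and characteristics and any deaths, and include them in an all-enrolled sensitivity analysis. Imputing them from navigated participants would credit them with the navigated change, so show a no-change assumption for them as well.

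No new survey of people who never started is needed. Its timing would be undefined in any case, because {18a} counts follow-up from the last navigation visit.

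The cost is a change of analysis wording and a few days of statistical work, with no new data. The downside is reliance on a stated assumption that the data cannot verify, and an estimate that may be somewhat smaller than the complete-case one.

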### Plans to give access to the full protocol, participant-level data and statistical code {31c}

Given the sensitive nature of the participant financial and clinical data to be collected in this trial, public access to participant-level data will not be permitted. However, upon request, data-sharing agreements to analyze de-identified, aggregated patient-level data will be permitted (discussed in further detail in “Availability of data and materials” section). Statistical code and additional information about the protocol may be requested from the UNC research team.

## Oversight and monitoring

### Composition of the coordinating center and trial steering committee {5d}

The UNC IRB is the central IRB (CIRB) of record for this study. We have completed all reliance paperwork required and, as part of the IRB application Multi-Site Study Information, Federal Assurance numbers were collected for all sites that have them. Each site has a designated Signatory Official and Contact person. In addition, the study has an External Advisory Board (EAB) that meets annually to provide expertise on rural health, dissemination and implementation of evidence-based interventions, qualitative methods, patient-centered cancer treatment decision-making, and cancer-related financial hardship. At the site level, oversight and monitoring occur monthly through efforts described previously.

### Composition of the data monitoring committee, its role, and reporting structure {21a}

As stated in the Further Guidance on a Data and Safety Monitoring for Phase I and Phase II Trials, an independent Data Safety and Monitoring Board may not be necessary or appropriate when the intervention is low risk, as is the case in this study. In this single-arm/non-randomized, Phase 2 clinical trial of a behavioral intervention with a very low risk for severe and unacceptable side effects, we follow NIH guidance and opted not to appoint a Data Safety and Monitoring Board. The PIs will provide continuous monitoring of patient safety in this trial.

Meetings/teleconferences will be held at a frequency dependent on study accrual, and in consultation with the study Biostatistician. At these meetings, the research team will discuss all issues relevant to study progress, including enrollment, safety, regulatory, data collection, etc. and the team will produce summaries or minutes of these meetings. These summaries will be available for inspection when requested by any of the regulatory bodies charged with the safety of human subjects and the integrity of data including, but not limited to, the oversight (Office of Human Research Ethics (OHRE) Biomedical IRB, the Oncology Protocol Review Committee (PRC) or the North Carolina TraCS Institute Data and Safety Monitoring Board (DSMB).

### Adverse event reporting and harms {22}

In the event that an unanticipated problem occurs at a site, the financial navigator will notify the PI at their site of the problem and appropriate referrals will be made to resolve the issue. The PI at the site will let the UNC PIs and the project manager know about the issue if appropriate. The project manager will log the event and share information with all sites within 24 h for severe complaints if appropriate.

### Frequency and plans for auditing trial conduct {23}

Each site will participate in two monthly video conferences and/or telephone calls (i.e., tailored technical assistance, group-based peer navigator support), and one annual in-person site visit with the UNC data management team to discuss accrual, retention, and compliance with forms. As an investigator-initiated study, this study will also be monitored generally by the Lineberger Comprehensive Cancer Center Data Safety and Monitoring Committee every twelve months.

### Plans for communicating important protocol amendments to relevant parties (e.g., trial participants, ethical committees) {25}

The UNC study coordinator will act as the liaison between participating institutions, the study, the PIs, and the CIRB. This person will be responsible for all protocol-related correspondence with the CIRB, and for relaying any official communications from the CIRB to the study team. If necessary, the project leads at each study site will communicate and relay information and documents between their local IRB and the CIRB.

The study coordinator will ensure that each site’s designated PI and financial navigator, receives a copy of the current study protocol, protocol amendments, and any other necessary study-related communication. Specifically, the study coordinator will send each site a copy of all protocol amendments within 7 days of approval of protocol changes and sites will be cc’d on study-related communications impacting their site.

### Dissemination plans {31a}

We understand and agree to comply with the NIH policy on Dissemination of Clinical Trial Information. The PIs and co-investigators acknowledge their willingness to share data and results with other eligible investigators through academically established means.

The clinical trial is posted on ClinicalTrials.gov, and the informed consent documents for this clinical trial will include a specific statement regarding the posting of trial information to the ClinicalTrials.gov website. Additionally, in concordance with NIH policy, the University of North Carolina at Chapel Hill is a registered Sponsor on ClinicalTrials.gov, and the UNC Office of Clinical Trials has named a Protocol Registration and Results System administrator to oversee registrations.

At study completion, we will disseminate our results via scientific journals and presentations, as well as through data briefs and other formats via the National Cancer Institute, the Cancer Prevention and Control Research Network (of which [name] is Coordinating Center PI), the American Cancer Society and Susan G Komen Foundation (through which Drs. [name] and [name] have ongoing partnerships), Livestrong, the American Psycho-Oncology Society, and the Association of Oncology Social Workers (through which [name] has ongoing partnerships). Additionally, we will leverage our existing statewide network of oncology practices and an expert advisory board to create and refine strategies to promote the implementation and effectiveness of FN to be disseminated to practices beyond the study context.

